#### **7.1.6.12 Engagement in Treatment**

Engagement in treatment is collected on the ETF eCRF at Day 7 as 'Yes' or 'No' depending on whether the participant reports receiving treatment for opioid use disorder on Day 7.

### **7.1.7 Analyses of Secondary Outcome Measures**

#### **7.1.7.1 Vital Signs**

Vital signs will be summarized with descriptive statistics at baseline, each post-injection time point, and change from baseline to each post-injection time point. Means values over time will be displayed graphically.

#### **7.1.7.2 Clinical Opiate Withdrawal Scale**

COWS will be analyzed in the same manner as vital signs.

#### **7.1.7.3 Objective Opiate Withdrawal Scale**

OOWS will be analyzed in the same manner as vital signs.

#### **7.1.7.4 Adjective Rating Scale for Withdrawal**

ARSW will be summarized with descriptive statistics at baseline, 240 minutes post-injection, and change from baseline to 240 minutes post-injection.

#### **7.1.7.5 Pupillary Diameter**

Pupillary diameter will be analyzed in the same manner as vital signs.

#### **7.1.7.6 Craving - Desire to Use Opioids**

Desire to use opioids will be summarized with descriptive statistics at baseline, each post-injection time point, and change from baseline to each post-injection time point. Mean values over time will be displayed graphically.

#### **7.1.7.7 Bad Drug Effects**

Bad drug effects will be summarized with descriptive statistics at baseline, 240 minutes post-injection, and change from baseline to 240 minutes post-injection.

#### **7.1.7.8 Pain Assessment**

Pain assessment will be summarized with descriptive statistics at each post-injection timepoint.

#### **7.1.7.9 Local Tolerability Scale**

Local tolerability will be summarized with descriptive statistics at each post-injection timepoint.

#### **7.1.7.10 Precipitated Withdrawals**

The number and percent of participants experiencing a precipitated withdrawal within 240 minutes post-injection will be presented.

#### **7.1.7.11 Satisfaction Questionnaire**

Satisfaction will be summarized with descriptive statistics.

#### **7.1.7.12 Engagement in Treatment**

The number and percent of participants engaged in treatment at Day 7 will be presented.

### **7.2 RCT Component**

#### **7.2.1 Definition of Primary Outcome Measure**

The primary outcome measure is engagement in formal addiction treatment for OUD at 7 days (Day 7). Formal addiction treatment is operationalized as those treatments consistent with the American Society of Addiction Medicine's levels of care (1 - 4) (Mee-Lee *et al.*, 2013).

The Engagement in Treatment: Patient (ETP) eCRF is where the participant self-reports whether they are in treatment for opioid use disorder on Day 7 (captured as Yes/No in the variable ETP.ETMEDTRT). If they report being in treatment, the participant then reports up to three different facilities where they received treatment on Day 7.

If a participant reports being in treatment on the ETP, the research team is expected to contact each facility listed on the ETP and complete the Engagement in Treatment: Facility (ETF) eCRF once for every facility listed on the ETP to verify the participant was in treatment. Among other questions (including whether the research team could contact and verify treatment), the ETF eCRF confirms whether the facility verified the participant was in treatment at that facility (captured as Yes/No in the variable ETF.ETENGAGE). If the facility verifies the participant was in treatment at that facility, the level of treatment the participant received at that facility is also captured (as No care received, Level I, Level II, Level III, Level IV, or Other in the variable ETF.ETCATGTR). If the facility reports a level of 'Other', they can specify further in free-text (captured in the ETF.ETCATSP variable).

The primary outcome is operationalized as follows:

- 1) A participant ***is engaged*** in formal addiction treatment at 7 days if the following is true:  
The participant self-reports being in treatment (ETP.ETMEDTRT = Yes) and at least one facility the participant reported being in treatment at verifies the participant was in treatment, at a level of Level I, Level II, Level III, or Level IV (ETF.ETENGAGE = Yes and ETF.ETCATGTR = [Level I, Level II, Level III, or Level IV]).
- 2) A participant ***is not engaged*** in formal addiction treatment at 7 days if one of the following are true:
  - a) The participant self-reports not being in treatment (ETP.ETMEDTRT = No).
  - b) The participant self-reports being in treatment (ETP.ETMEDTRT = Yes) and all facilities are contacted and report the participant as not being in treatment (ETF.ETENGAGE = No).

For all other scenarios, the primary outcome is considered missing. Note this includes (but is not limited to) the following:

- The participant was not reached or otherwise did not self-report whether they are in treatment (i.e., ETP.ETMEDTRT is missing)
- A facility the participant reported being in treatment at (on the ETP eCRF) does not have a corresponding ETF eCRF filled out for that facility (including if a facility declines to verify engagement)
  - Unless one other facility reported by the participant verifies they were engaged in treatment at a level of Level I, Level II, Level III, or Level IV (so that the participant is engaged in treatment because criterion (a) above is achieved, even though not all ETF eCRFs are completed)

Note that participants incarcerated or hospitalized on Day 7 or 30 may meet this operationalized definition as well if receiving MOUD.

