#### 8.4.6 7-day Follow-up Assessments

Follow-up assessments are expected to be conducted at 7 days post enrollment via telephone by the ED study staff. Assessment of engagement in formal addiction treatment on the 7th day after enrollment will be based on direct contact with the treatment provider/program provided by the

participant and or referral noted in the EHR. Printed reminders for the follow-up assessment will be given to the study participant prior to ED discharge. In addition, the RA will send a reminder in the mail/text/email/or social media (based on study participant preference) about 3 days prior to the scheduled follow-up with an additional reminder notification via mail/text/email/or social media (based on study participant preference) the day before the scheduled follow-up.

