### 12.3 Sample Size Justification for Evaluation of Effectiveness

For the comparison of XR vs. Standard SL-BUP, the primary effectiveness outcome will be engagement in formal addiction treatment at 7 days, classified as engaged or not engaged based on verification with the treatment provider. A sample size of 850 per group is required to ensure 90% power at the 2-sided 0.05 significance level to detect a difference in the proportion engaged of 8% between SL and XR-BUP (i.e., 45% engaged in SL vs. 53% engaged in XR-BUP). We will enroll approximately 2000 patients to accommodate a 15% dropout. Figure 6 below shows the sensitivity of the power of the study given variations in the proportions of those engaged in treatment. Regardless of the proportion engaged in treatment in the SL group, our sample size will provide > 90% to detect improvements for the XR group of 8% and > 80% to detect improvements of 7%. This sample size will also provide sufficient power to detect differences in notable subgroups (treatment seeking, rural/urban, insurance Y/N).

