(MCAR). Robins, Rotnitzky and Zhao proposed an extension of GEE called the weighted GEE to alleviate this restrictive assumption. The weighted GEE provides consistent parameter estimates when the dropout mechanism is correctly classified by implementing the inverse-probability weighted method to account for dropouts under the missing at random (MAR) assumption. Inverse probability weights are estimated by a logistic regression of dropout at a particular measurement occasion. The dropout model will include baseline demographic and clinical characteristics including treatment engagement prior to enrollment, site, treatment group, insurance status and time as well as outcomes at previous timepoints. From the dropout model, predicted probabilities of dropout will be estimated for each subject at each post-randomization timepoint. The predicted probabilities will then be translated into weights where the weight is the inverse of the cumulative probability of dropping out at a particular assessment. Prior to final analysis, weights will be evaluated for outliers ( $>3$ ). If identified, additional covariates in the logistic model and/or trimming of weights will be considered to correct for this. The weighted GEE model will contain an effect for intervention (XR vs. SL). An exchangeable working correlation will be used to account for clustering responses from the same participants (i.e., 7 and 30 days). The model will also include treatment engagement in prior 12 months from baseline, age, sex, ethnicity/race, insurance status and site (see **Exhibit 2** below). Linear contrasts will be used to estimate odds ratios, treatment differences and 95% confidence intervals for the proportions of participants that engage in treatment in XR vs. SL at both 7- and 30-days follow-up.

The following SAS System code will be used for the GEE analyses. The variables in the models are as follows:

- *primdat*: primary outcome analysis file,
- *patid*: patient ID,
- *site*: site ID,
- *site2*: site ID with small sites ( $\leq 20$  randomized) pooled into one site,
- *treat*: treatment arm - XR-BUP or SL-BUP,
- *engage*: engagement variable where 1 = engaged and 0 = not engaged,
- *exist*: 1 if *engage* is not missing and 0 if *engage* is missing,
- *visit*: study visit (Day 7 or Day 30),
- *gender*: categorical variable for gender,
- *race\_cat*: categorical variable for White, Black, Other race, unknown or not reported,

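### Among participants who answer the Day 7 treatment question, only those who say Yes can have a missing primary outcome, and the planned weights ignore that answer

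*Combined protocol and SAP*

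**What the plan says.** SAP 7.2.1 builds the primary outcome from two forms: the participant's own report (ETP) and the facility's report (ETF).

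- **Engaged:** the participant says Yes and at least one named facility verifies treatment at Level I to IV.
- **Not engaged (a):** "The participant self-reports not being in treatment (ETP.ETMEDTRT = No"). No facility is contacted.
- **Not engaged (b):** the participant says Yes and every named facility is contacted and denies treatment.
- **Missing:** "For all other scenarios, the primary outcome is considered missing". The listed examples are a participant who was not reached or gave no answer, and a named facility without a completed ETF form, "including if a facility declines to verify engagement". An exception applies if another named facility verifies Level I to IV.

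Once a facility verifies treatment, the level is captured "as No care received, Level I, Level II, Level III, Level IV, or Other in the variable ETF.ETCATGTR". Neither *No care received* nor *Other* satisfies the engaged rule or the not-engaged rule, so both fall into missing unless another facility verifies Level I to IV.

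For the weights, SAP 7.2.2 states: "The dropout model will include baseline demographic and clinical characteristics including treatment engagement prior to enrollment, site, treatment group, insurance status and time", plus outcomes at previous timepoints. At Day 7 there is no previous follow-up outcome. The Day 7 code uses arm, pooled site, age, gender, race, ethnicity and insurance, with prior engagement commented out. The Day 7 self-report is in neither the text nor the code. SAP 7.2.7 declares the analysis valid under MAR and says that an MNAR analysis may be done, with no scenario specified.

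**The concern.** Among participants who answer the Day 7 question, the probability of a missing outcome is zero after No and above zero after Yes whenever any Yes goes unresolved. Everyone who can be scored engaged is in the Yes group. Missingness therefore depends on a recorded variable that is close to the outcome itself, and the weight model does not contain it. MAR given that model then fails, and the resolved sample under-represents engaged participants.

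At stake are the arm-specific engagement proportions and their difference, which SAP 7.2.2 promises to report with confidence intervals. If verification succeeds more often in one arm, the primary odds ratio is at stake too. The Day 30 outcome uses the same definition, and engagement in MOUD (SAP 7.2.4.1) has the same asymmetry. The GLMM sensitivity analysis in SAP 7.2.3 reuses the same weight, so it would not reveal the problem.

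**Working it through.** **The plan's own figure.** Protocol 12.3: "A sample size of 850 per group is required to ensure 90% power" "at the 2-sided 0.05 significance level", for 45% (SL) against 53% (XR). The two-proportion formula gives 819 per arm, or 844 with continuity correction, which is within 1% of 850. Power at 850 per arm is about 91%. Allowing 15% dropout, 850/0.85 = 1,000 per arm, or 2,000 in total. The planned odds ratio is (0.53 × 0.55)/(0.45 × 0.47) = 1.378.

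**Assumptions.** p is the true engagement rate. A share v of the engaged says Yes but cannot be verified. Everyone not engaged is classified. 850 per arm answer the question. The documents give no v, so a range is shown.

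**Formula.** Observed rate = p(1 − v)/(1 − pv). Observed odds are therefore the true odds × (1 − v), and

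observed OR = true OR × (1 − v_XR)/(1 − v_SL).

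**Equal v.** The ratio is 1, so the odds ratio stays at 1.378. For v = 15% in SL: 0.45 × 0.85/(1 − 0.0675) = 0.3825/0.9325 = 41.0%.

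| v | SL | XR | Difference (points) | OR | Power |
|---|---|---|---|---|---|
| 0% | 45.0% | 53.0% | 8.0 | 1.378 | 91.1% |
| 5% | 43.7% | 51.7% | 8.0 | 1.378 | 90.4% |
| 15% | 41.0% | 48.9% | 7.9 | 1.378 | 88.7% |
| 30% | 36.4% | 44.1% | 7.7 | 1.378 | 85.0% |

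Power at v = 15%: 850 × (1 − 0.0675) = 792.6 SL and 850 × (1 − 0.0795) = 782.4 XR outcomes are resolved. The SE is 2.50 points, 7.92/2.50 = 3.17, and Φ(3.17 − 1.96) = 88.7%.

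**Unequal v, no true effect (45% in both arms).**

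- v = 10% SL, 15% XR: 42.4% against 41.0%, OR 0.944. The difference is −1.39 points with SE 2.46, ratio −0.56. Two-sided rejection = Φ(−1.40) + Φ(−2.52) = about 8.7%.
- v = 10% SL, 20% XR: 42.4% against 39.6%, OR 0.889. The difference is −2.85 points with SE 2.47, ratio −1.15. Rejection is about 21%.

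Swapping the arms gives the same rejection rates with ORs of 1.059 and 1.125. Only that direction would produce a false claim for XR.

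**Unequal v, true OR 1.378.** 10%/20% (SL/XR) gives 1.378 × 0.80/0.90 = 1.23 and power of about 52%. 20%/10% gives 1.55.

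**Do the planned weights repair this?** A simulation used 200,000 participants per scenario, 10% not reached, 5% of the non-engaged falsely saying Yes, and verification failing at random among Yes reports within each arm.

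| v (SL/XR) | Full data | Planned weights | Two-step weights |
|---|---|---|---|
| 15%/15% | OR 1.36 (45.4%/52.6%) | OR 1.36 (41.8%/48.9%) | OR 1.36 (45.4%/52.6%) |
| 10%/20% | OR 1.39 (45.2%/52.9%) | OR 1.23 (42.9%/47.8%) | OR 1.38 (45.3%/52.8%) |
| 20%/10% | OR 1.38 (45.2%/52.9%) | OR 1.54 (40.4%/50.5%) | OR 1.38 (45.3%/52.9%) |

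The two-step weights model answering first, then resolution given Yes. They succeed here partly because the simulation makes unverified Yes resemble verified Yes.

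**The case against.** The strongest reply is that the primary test is on the odds ratio, which an equal unverified share leaves untouched. That stands. Nothing in the documents shows that v differs by arm: protocol 8.4.13 says that referral will be identical for both arms. Where participants actually attend could still differ, but that is a possibility only.

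The plan also has features that should keep v small. Unwillingness to allow contact with the referral provider is an exclusion (protocol 8.3.2), consent covers such contact (14.4), and up to three facilities can be named with one confirmation sufficing. The list of RCT tables in SAP 16.2 includes primary outcome availability by arm, which would expose an imbalance. These features limit the harm or reveal it; they do not correct the arm rates. The MNAR analysis could help, but it is optional and unspecified. By contrast, the ancillary component commits to worst-case imputation, with complete-case and best-case analyses above 5% missing (SAP 7.1.1 and 7.1.4).

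A reader might go further and say that unreached participants should be scored through the facility on record, because protocol 8.4.6 allows Day 7 engagement to rest on contact with the provider supplied by the "participant and or referral noted in the EHR". The documents do not support that as a safe repair. Protocol 12.2 describes verification of self-reported engagement, the Day 30 procedure (8.4.7) has no EHR route, and one referral facility's denial would misclassify anyone treated elsewhere.

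**Conclusion.** The point holds for the arm rates and their difference. As written, the rule and the weight model together bias engagement downward in both arms whenever some true Yes reports go unverified: by about 1 point at v = 5%, 4 points at 15% and 9 points at 30%. With equal v, the cost to the primary test is a modest loss of power, from about 91% to 88.7% at v = 15% if 850 per arm answer. All sizes rest on an assumed v.

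Four stronger readings are tempting but not supported:

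- *The primary test is invalid.* This needs v to differ by arm. A 5-point gap gives about 8.7% type I error and a 10-point gap about 21%; neither gap comes from the documents.
- *Missingness depends on the outcome itself.* It depends on the self-report. False Yes reports can also go unverified, and a reached participant who gives no answer is missing as well.
- *Weighting cannot help.* The planned weights do not help, but the self-report is recorded for everyone who answers and can be used.
- *The sample size re-estimation is undermined.* It was designed to update only the control rate. At v = 15%, required n per arm (without continuity correction) moves only from 819 to 811.

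**What to change.** Make three changes in SAP v4.0, which the revision history in SAP 14 reserves for finalising the RCT sections before database lock.

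1. **Two-step weight.** Set the Day 7 probability to P(answers | baseline covariates, arm, site) × P(resolved | self-reported Yes, arm, site, baseline covariates), with the second factor equal to 1 for self-report No. Do the same at Day 30.
2. **Facility codes.** Classify *Other* by reviewing its free text blind to arm. Query *No care received* when it appears with ETENGAGE = Yes, since the two entries conflict. Score it not engaged if confirmed at all named facilities.
3. **Two committed bounding analyses.** Score all unverified Yes as engaged, then all as not engaged. They are needed because the two-step weight still assumes that unverified Yes resemble verified Yes. At v = 15% in both arms, under the assumptions used above, the bounds would be 45%/53% and 38.3%/45.1% (0.45 × 0.85 and 0.53 × 0.85).

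The cost is SAP wording, programming, a blinded review of free text and some site queries. The self-report, facility, facility contact log and facility refusal forms already exist, so no new participant data are needed.

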#### 8.1.1 Hypothesis 2a (Primary Effectiveness Outcome)

*XR-BUP will result in more patients engaged in formal addiction treatment at 7 days*

The rates of engagement in formal addiction treatment at 7 days will be compared by treatment arm. Engagement in formal addiction treatment will be defined as enrollment and receiving formal addiction treatment at 7 days, confirmed by contact with the facility and/or treating clinician. Formal addiction treatment will be operationally defined as those treatments consistent with the American Society of Addiction Medicine's levels of care (1-4) and can include a range of clinical settings including office-based providers of BUP or naltrexone, OTPs, intensive outpatient, inpatient, or residential treatments. Patients do not need to be receiving MOUD at 7 days to be considered engaged in formal addiction treatment. Participation in a mutual-help program such as Alcoholics Anonymous (AA) or Narcotics Anonymous (NA) alone will not be considered as engagement in formal addiction treatment. Additional analyses evaluating the effects of patient and site characteristics will also be conducted.

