#### 8.4.7 30-day Follow-up Assessments

Follow-up assessments are expected to be conducted at 30-days post enrollment via telephone by the ED study staff. Assessment of engagement in formal addiction treatment on the 30th day after enrollment will be based on direct contact with the treatment provider/program provided by the participant. Printed reminders for the follow-up will be given to the study participant prior to discharge. In addition, the RA will send a reminder in the mail/text/email/or social media (based on study participant preference) about 7 days prior to the scheduled follow-up with an additional reminder phone call the day before the scheduled follow-up.

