Once eligibility is determined, the Research Assistant (RA), who is knowledgeable about the study will explain the significant elements of the study to the potential participant. Included in the consent will be language allowing the RA to contact community-based providers and programs to determine the patient's engagement in formal addiction treatment after trial enrollment. If the patient is able to converse and alert to person, place and time, the RA obtains signed, dated consent. A copy of the signed consent will be left with the participant. All persons obtaining consent must have completed appropriate training. The participant will be informed that their participation is voluntary, and they may withdraw from the study at any time, for any reason without penalty. Individuals who refuse to participate or who withdraw from the study will be treated without prejudice. Study sites will be responsible for maintaining signed consent forms as source documents for quality assurance review and regulatory compliance.

The informed consent form must be updated or revised whenever important new safety information is available, or whenever the protocol is amended in a way that may affect participants' participation in the study.

For this study, there will be three written consents: Two for the ancillary study for patients with COWS < 8 and COWS ≥ 8 and one for the main trial comparing SL-BUP with XR-BUP.

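### The SAP's primary outcome requires a self-report, so referral-clinic information can never count for unreached participants, deaths have no rule, and the protocol's own sections conflict on this

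*Combined protocol and SAP*

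**What the plan says.** **SAP 7.2.1.** A participant is engaged if they report being in treatment and at least one facility they named verifies it at Level I to IV. They are not engaged if they report no treatment, or if they report treatment and every facility denies it. Every other case is missing, and the first example given is: "The participant was not reached or otherwise did not self-report whether they are in treatment". Death is not mentioned.

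**Protocol sections that rest on the facility.** Section 8.1.1 defines engagement as enrolled and receiving treatment, "confirmed by contact with the facility and/or treating clinician", with no self-report condition. Section 8.4.6 bases the Day 7 assessment on direct contact with the programme given by the "participant and or referral noted in the EHR". Unwillingness to permit contact with the referral provider is an exclusion (8.3.2, item 11), and 14.4 puts into the consent "language allowing the RA to contact community-based providers and programs to determine the patient's engagement in formal addiction treatment after trial enrollment".

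**Protocol sections that start from self-report.** Sections 8.8.1 and 12.2 have the participant report first and the provider verify afterwards.

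**Day 30.** Under 8.4.7 the assessment "will be based on direct contact with the treatment provider/program provided by the" participant. The EHR route is absent.

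**Missing data.** SAP 7.2.2 uses inverse-probability weighting under missing at random. SAP 7.2.7 makes a missing-not-at-random analysis optional. Deaths appear only as a safety listing (SAP 8.2.6).

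**The concern.** The protocol secured permission to ask the referral clinic directly, and at Day 7 it says how to find that clinic. The SAP then gives the clinic's answer no role unless the participant has spoken first. A participant who attends the referral clinic but never completes the patient form is missing, whatever the clinic would say.

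Whether someone can be reached may depend on whether they are in treatment, and in an open-label trial that dependence may differ between arms. Weights built from baseline covariates cannot remove dependence on the unobserved Day 7 outcome. As coded in SAP 7.2.2, the Day 7 weight model contains arm, site, age, sex, race, ethnicity and insurance, with prior engagement commented out. What is at stake is a bias in the primary comparison that the planned analyses need not reveal.

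Death is a separate gap. Someone who died on or before Day 7 cannot be engaged on Day 7, yet the analysis lets similar survivors stand in for them.

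**Working it through.** **Inputs.** From protocol 12.3: "A sample size of 850 per group is required to ensure 90% power at the 2-sided 0.05 significance level"; rates, "i.e., 45% engaged in SL vs. 53% engaged in XR-BUP"; and "We will enroll approximately 2000 patients to accommodate a 15% dropout". Allocation is 1:1 (8.4.4). The reach probabilities, death counts and recovered shares below are assumptions; the documents give none.

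**1. The plan's own figures.** For two proportions, n per arm = [1.96·√(2·p̄·q̄) + 1.2816·√(p₁q₁ + p₂q₂)]² / (p₂ − p₁)², with p̄ = 0.49. This is (1.3856 + 0.9031)² / 0.0064 = 819, or 844 with continuity correction. At 850 per arm, z = (0.08·√850 − 1.3856) / 0.7047 = 1.34, so power is 91.0%. 1700 / 0.85 = 2000. The planned size is sound, and this point does not depend on an error in it.

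**2. Bias when reach depends on engagement.** Take a true null: 45% engaged in both arms, 1000 per arm, 15% unreached in each. If a share a of the engaged and b of the not engaged are reached, the observed rate is 0.45a / (0.45a + 0.55b). Each pair below keeps total reach at 85%.

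| Reach: engaged / not engaged | Observed rate |
|---|---|
| 85% / 85% | 0.3825 / 0.850 = 45.0% |
| 90% / 80.9% | 0.4050 / 0.850 = 47.65% |
| 95% / 76.8% | 0.4275 / 0.850 = 50.3% |

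With about 850 observed per arm, the standard error of the difference is about 0.0242. Rejection is the two-sided 5% rate.

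| SL-BUP reach | XR-BUP reach | False difference | Rejection |
|---|---|---|---|
| 95% / 76.8% | 95% / 76.8% | 0 | 5% |
| 90% / 80.9% | 95% / 76.8% | +2.65 points | about 19% |
| 85% / 85% | 95% / 76.8% | +5.3 points | about 59% |

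Swapping the arms reverses the sign. The calculation is unweighted.

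**3. Deaths.** With d deaths per 1000 scored as not engaged, a 45% rate becomes 0.45·(1000 − d)/1000. For d = 2, 5 and 10 this is 44.9%, 44.8% and 44.6%, a shift of at most 0.45 points.

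**4. Would recovering unreached participants raise power?** Keep 45% and 53% among the 850 reached per arm.

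| Rates among those recovered (SL / XR) | Half recovered (925 per arm) | All recovered (1000 per arm) |
|---|---|---|
| 45% / 53% | 93.1% | 94.8% |
| 20% / 25% | about 92% | about 92.5% |
| Equal in both arms (10%, 20% or 30%) | about 89% | 86% to 87% |

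In the last row the difference shrinks to 850 × 8 / 925 = 7.35 points with half recovered, or 850 × 8 / 1000 = 6.8 points with all. Power can go up or down, so no gain is claimed.

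**The case against.** The strongest reply is that SAP 7.2.1 follows protocol 12.2, the statistical section's own definition, and 8.8.1; both begin with self-report. That stands. A reader might infer that the SAP simply departs from the protocol. The documents do not support that: the protocol conflicts with itself, and the SAP follows one side of the conflict.

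A reader might also infer that the endpoint was designed not to depend on reaching the participant by telephone. No section says so. Section 8.4.6 expects telephone follow-up, the eligibility criteria require two further contact numbers, and the locator form collects family and friends' details. Nor does a lost telephone by itself make the outcome missing, because SAP 3.2.2.3 allows the visit to take place after Day 7.

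Third, it is tempting to let the referral clinic settle the primary outcome outright. For participants who report treatment, the SAP requires every named facility (up to three) to deny it. One referral clinic's denial is weaker evidence, because the participant may be treated elsewhere. Identical referral in both arms does not guarantee equal attendance elsewhere in an open-label trial. This objection stands and shapes the fix.

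Finally, some protection exists: weighting, a table of outcome availability by arm, and a listed table of sensitivity analyses. None of it requires facility information on unreached participants, and the only analysis aimed at missing-not-at-random data is optional.

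**Conclusion.** The point holds in limited form. SAP 7.2.1 makes self-report a precondition for any outcome value, so referral-clinic information cannot count for unreached participants and deaths before Day 7 are treated as missing. Protocol 8.1.1 and 8.4.6 point one way and 8.8.1 and 12.2 the other; they must be reconciled.

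The consequence is reliance on missing at random, with possible bias. Under the assumed patterns the false difference is 2.65 to 5.3 points against an 8-point target. It is zero if reach depends on engagement in the same way in both arms. These are illustrations of scale, not estimates for this trial. The effect of deaths is tenths of a point; a rule for them is a matter of coherence. A reader might infer that the trial is underpowered or that recovery would add power. Neither is established.

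The sample-size re-estimation (SAP 11.3) uses only SL-BUP participants with non-missing outcomes, so it inherits the same definition.

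**What to change.** 1. In SAP 7.2.1, class a death on or before the target day as not engaged, at Day 7 and at Day 30.
2. When the patient form is missing, complete the facility form with the referral programme recorded in the EHR, as protocol 8.4.6 already provides for at Day 7.
3. Make a facility-based analysis of unreached participants a required sensitivity analysis. Score Level I to IV verification as engaged. Score a referral-clinic denial once as not engaged and once as missing. A clinic that cannot be contacted or declines leaves the outcome missing. Report missingness by arm and by reason.
4. Reconcile protocol 8.1.1, 8.4.6, 8.8.1 and 12.2 with SAP 7.2.1, and settle whether 8.4.7 should carry the EHR route at Day 30.

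**Cost.** At the planned 15%, this means calls for about 0.15 × 2000 = 300 participants at Day 7, and a similar number at Day 30 if the route is added there. The facility form is now triggered by the patient form, so completion instructions change as well as SAP text. Some participants treated elsewhere may be misclassified; scoring denials both ways would expose that. The SAP calls its RCT section a draft, to be finalised in version 4.0 before database lock, which is the natural place for these changes.
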